### Interventions

2.12.

Placebo group participants will receive an intravenous infusion of 0.9% normal saline (Weigao Group Co., Ltd., Weihai, Shandong, China). The infusion pump (Henan Tuoren Medical Equipment Group Co., Ltd., Changheng, Henan, China) mode is constant speed pumping, and the pumping time is from the end of the intraspinal anesthesia administration to the knee joint suture. The anesthesiologist can choose the appropriate medication protocol according to clinical practice, but other NMDA receptor antagonists, such as dextromethorphan and amantadine, will not be used.

Esketamine group participants will receive an intravenous infusion of esketamine (Jiangsu Heng Rui Medicine Co., Ltd., Jiangsu, China) following a standard dilution protocol [2 ml (50 mg) esketamine with 0.9% normal saline to 20 ml, 2.5 mg/ml]. The infusion rate of esketamine is 0.3 mg/kg/h, the mode of the infusion pump is constant speed pumping, and the infusion time is from the end of the spinal anesthesia administration to the knee joint suture. Drug managers need to monitor that the maximum dose of esketamine is not more than 0.5 mg/kg.

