### Adverse event reporting

3.5.

AE in this trial include any adverse symptoms, abnormal physical signs, and abnormal experimental results after the intervention, regardless of whether there is a causal relation with the intervention. Any AE, including those described by the participant or obtained through investigator inquiry or physical examination, laboratory examination, or other examination methods, will be recorded, actively managed, and closely tracked until the condition is relieved or stable. The investigator will track all AE and record them in the standard paper case report form (CRF), including their detailed content, location, time, severity, treatment measures, and treatment results.

SAE refers to death, life-threatening, severe disability or loss of function, need for hospitalization or prolonged hospitalization, and other critical medical events after the participants receive the intervention. Should a SAE occur, all rescue efforts will be made and necessary measures taken to actively avoid permanent damage. The investigator will notify the person in charge, the clinical trial organization, and the ethics committee by telephone or fax within 24 h and record the SAE details in the CRF.

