## Data collection

4.

An investigator ([name], [name], or [name]) will conduct a preoperative visit with eligible participants the day before their surgery. Baseline data, recorded from participant self-report and their electronic medical records, will include age, sex, height, weight, ASA grade, complications, duration of analgesic use, admission time, and preoperative blood glucose and cortisol concentration. The NRS will be used to assess baseline pain. The Timed Up and Go test will be used to evaluate baseline knee function and active and passive knee flexion. Preoperative baseline recovery quality score will be evaluated using the QOR-15. The anesthesiologist will collect and record intraoperative data through the anesthesia management system, including dosages of sedatives and analgesics, steroid use (yes/no), blood loss, infusion volume, tourniquet use time, operation time, and any AE. An investigator ([name], [name], [name], or [name]) will collect postoperative data, including pain-related indicators, opioid consumption, knee joint function recovery indicators, and any AE. Postoperative data will be collected from the doctor and nurse management stations of the hospital information system, standardized CRF, and PCIA information storage cards (Table 1). Outcome assessors will have been trained in the standard operating procedures of clinical drug trials. The clinical data monitoring committee (DMC) will supervise all data collection to ensure reporting accuracy, integrity, readability, and timeliness. All source files will be rigorously cleaned to ensure accurate data use.

**Table 1 tab1:** Study protocol.

Outcome measure	Visit 1	Visit 2	Visit 3	Visit 4	Visit 5	Visit 6	Visit 7
Time	1 day pre- surgery	During operation	PACU	Within 12 h post-surgery	POD 1	POD 2	Hospital discharge
Eligibility screening	X	–	–	–	–	–	–
Informed consent	X	–	–	–	–	–	–
Demographic characteristics	X	–	–	–	–	–	–
Preoperative education	X	–	–	–	–	–	–
Baseline measures	X	X	–	–	–	–	–
Randomization	X	–	–	–	–	–	–
Intervention	–	X	–	–	–	–	–
Incidence of rebound pain	–	–	–	X	X	–	–
First time to begin pain cycle	–	–	–	X	X	–	–
First time rebound pain occurred	–	–	–	X	X	–	–
NRS scores	X		X	X	X	X	–
Cumulative opioid consumption	–	X	X	X	X	X	–
Timed Up and Go test	X	–	–	–	X	–	–
Range of motion of knee joints	X	–	–	–	X	–	–
Time to reach discharge standard	–	–	–	–	–	–	X
Length of stay	–	–	–	–	–	–	X
Blood glucose and cortisol concentration	X	–	–	–	X	–	–

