## Statistical methods

7.

We plan to include data from all the participants assigned to randomized grouping, regardless of intervention, in a intention-to-treat analysis. SPSS version 25.0 will be used to analyze data. The Shapiro–Wilk test will be used to assess normality of continuous variables. Normal data will be described as means ± standard deviations, and otherwise as medians and interquartile ranges. Demographic and intraoperative data will be compared by independent samples *t*-tests, Mann–Whitney U test, chi-square test, Yates’ chi-square test, or Fisher’s exact probability test, as appropriate. The primary study outcome (rebound pain) is dichotomous, and the relative risk (RR) and 95% confidence interval (CI) will be calculated using the modified Poisson regression model for the esketamine and placebo groups. We plan to evaluate three modified Poisson regression models: model 1 will be unadjusted; model 2 will be adjusted for gender, age, BMI, ASA grade, complications, long-term analgesics use, and baseline pain score; model 3 will be adjusted for tourniquet use time, operation time, steroid use (yes/no) and analgesic and sedative doses during the operation. We plan to conduct a sensitivity analysis on the primary outcome. The effects of the intention-to-treat set and the per-protocol set on the consistency of the primary outcome will be compared. The per-protocol set will be whether the participant has completed all main baseline variables, has not violated the inclusion or exclusion criteria, has completed all trials and assessments, and was in good adherence. Second, we plan to compare the impacts of different statistical methods (i.e., stratified chi-square test and modified Poisson regression model) on the consistency of the primary outcome. Stratified chi-square analysis adjusted for major potential confounders, i.e., age, sex, use of steroids (yes/no), preoperative pain score, and long-term use of analgesics (yes/no) before surgery. Adjusted OR values will be calculated using the Cochran–Mantel–Haenszel test (CMH).

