Secondary outcomes will be exploratory, without adjustment for multiple comparisons. The first time to enter the pain cycle within the first 24 postoperative hours and the first time to rebound pain within the first 24 postoperative hours will constitute the survival data. Kaplan–Meier survival curves and log-rank tests will be used to analyze survival data, and univariate COX regression will be used to calculate HR and 95% CI. NRS and opioid use at different postoperative intervals will constitute repeated-measurement data. Generalized estimation equation (GEE) will be used, with patient identification number as the main variable, time as the main internal variable, and NRS and opioid consumption as the dependent variables. Independent samples *t*-tests or Mann–Whitney U tests will be used to compare independent data between the groups. The Hodges–Lehmann method will be used to evaluate the pseudo-median differences and 95% CI. Categorical data will be expressed as the number of cases (percentage) and analyzed using the chi-square test, Yate’s chi-square test, or Fisher’s exact probability test. Safety outcomes will be analyzed using the safety analysis dataset. All participants who undergo randomization and for whom post-trial safety evaluation data are available will be included in the safety analysis dataset. All statistical tests will be two-sided and *p* < 0.05 will be considered statistically significant.

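### The safety set is fixed by randomization and data availability, not by receipt of the infusion, so an operated but uninfused participant can enter it; the effect is probably small

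*Protocol article*

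**What the plan says.** Section 7 (Statistical methods) defines the safety set by two conditions, randomization and availability of data: "All participants who undergo randomization and for whom post-trial safety evaluation data are available will be included in the safety analysis dataset".

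Other sections bear on this rule:

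- **Timing of randomization.** Table 1 (section 4) puts randomization at Visit 1, one day before surgery, and the intervention at Visit 2, during the operation.
- **Timing of the infusion.** Section 2.12 states for the placebo arm that "the pumping time is from the end of the intraspinal anesthesia administration to the knee joint suture", and gives the same timing for esketamine.
- **Events.** Section 3.5 defines an adverse event as "any adverse symptoms, abnormal physical signs, and abnormal experimental results after the intervention". Its list of serious events ends with "other critical medical events after the participants receive the intervention".
- **Participants without the intervention.** For efficacy, section 7 says: "We plan to include data from all the participants assigned to randomized grouping, regardless of intervention, in a intention-to-treat analysis". The plan thus allows for participants who are randomized but do not get the assigned treatment.
- **Collection of safety data.** The last row of Table 1 has safety outcomes collected over the whole study up to discharge, and does not tie collection to the infusion.

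**The concern.** A safety population is meant to show what happens to people exposed to the study drug. This one is defined by assignment and then filtered on whether later data exist, so it follows neither randomization nor exposure.

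Two errors are possible. First, a participant who has the operation but not the infusion has inpatient safety data, so both conditions are met and that person is counted. Under section 3.5 the same person cannot have a qualifying event, because there was no intervention for it to follow. The numerator and the denominator then obey different rules. Second, an infused participant without later safety data is removed. Such a loss need not be random: section 2.4 names a severe adverse event as a ground for withdrawal, and section 7.1 names side effects among the causes of missing data.

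For harms caused by esketamine itself, such as delirium or nightmares, both errors can lower the reported rate in the esketamine arm.

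**Working it through.** **Can an uninfused participant qualify?** Take someone randomized the day before who is operated on, but for whom the infusion is never started.

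1. Randomized: yes (Table 1, Visit 1).
2. Safety data available: yes on a plain reading. Section 3.4 requires monitoring in the PACU and on the ward for a minimum of 24 hours, and Table 1 collects safety outcomes up to discharge.
3. Exposed: no.
4. Able to have an adverse event as section 3.5 defines it: no.

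This person is in the denominator and cannot be in the numerator.

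**Size.** The plan states no figure for the safety set. The only planned number used here is the arm size, which reproduces from section 2.6: 160 / (1 − 0.10) = 177.8, rounded up to 178.

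Inputs:

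- n = 178 per arm (section 2.6).
- r = 12%, the true event rate among infused participants. This is an assumption. The figure appears in the dose rationale of section 2.12 as a rate of adverse mental reactions at high doses, so it serves only as an illustration.
- u = number uninfused in the arm. The documents give none. The assumed range is 0 to 18, about 0 to 10% of the arm. The upper end borrows the whole withdrawal allowance, which was not set for this purpose.
- r0 = rate of counted events among the uninfused.

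Reported rate = [(n − u) × r + u × r0] / n.

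If section 3.5 is applied strictly, r0 = 0 and the formula becomes r × (n − u) / n:

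| u | Calculation | Reported rate |
|---|---|---|
| 0 | 0.12 × 178/178 | 12.0% |
| 2 | 0.12 × 176/178 | 11.9% |
| 4 | 0.12 × 174/178 | 11.7% |
| 9 | 0.12 × 169/178 | 11.4% |
| 18 | 0.12 × 160/178 | 10.8% |

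These reductions are upper bounds for each u, because an uninfused participant enters only if safety data exist. A set based on exposure gives 12.0% in every row.

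**Direction.** The rate falls only when r0 is below r. Section 3.3 also lists nausea, hypotension, bradycardia, nerve injury from the block, wound infection and thrombosis. If these are tabulated from the Table 1 collection rather than under section 3.5, operated but uninfused participants can contribute events. Then r0 is above zero, and with r0 = r nothing changes. If r0 exceeds r, the reported rate rises.

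**The case against.** The strongest reply is that the data condition already does the filtering. The term post-trial may be meant as after the trial treatment, in which case someone never infused has no such data and is excluded. That reading is possible, but the article does not state it, and an ambiguous population definition needs correcting anyway.

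A reader might infer more than the documents support, and on these points the reply stands:

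- **Every uninfused participant is counted.** Not so. A cancelled operation would usually leave no postoperative safety evaluation, and the second condition would remove that person. The case that matters is surgery without the infusion, and nothing suggests more than isolated instances with a single intraoperative infusion given the day after randomization.
- **Adverse event rates are always pulled toward zero.** Not so. This holds for events counted strictly under section 3.5 and is plausible for esketamine-specific harms. It is not established for block- or surgery-related events.
- **A participant given the wrong syringe is counted in the wrong arm.** The article does not say how such a person is grouped. That detail is commonly left to the statistical analysis plan, and silence here is no fault. Section 2.13 also has three staff members check group, dose and pump speed.
- **Many infused participants will be dropped.** This is unlikely. Intraoperative adverse events are recorded (section 4) and monitoring continues on the ward, so an infused inpatient with no safety data at all should be rare.

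What the reply does not remove is that the stated rule omits exposure and adds a condition on data that arise after treatment.

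**Conclusion.** The point holds as a minor defect in a definition that the article states outright. The safety set can include operated but uninfused participants and can exclude infused ones, while adverse events are counted only after the intervention.

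The expected effect is small: on the illustrative 12%, at most about 0.1 percentage points with 2 uninfused participants in the arm and 0.6 points with 9. These sizes rest on an assumed event rate, assumed uninfused counts and no counted events among the uninfused. They are not forecasts for this trial. The documents do not support a claim that the safety comparison as a whole is biased in a known direction. The sample size and the primary analysis are not affected.

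**What to change.** Replace the safety-set sentence in section 7 with one based on exposure: all participants who received any amount of the study infusion (esketamine or saline), with no condition on later safety data, analyzed by the infusion actually received. The last clause is added to complete the definition, since a set based on exposure should also say how participants are grouped.

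The denominator then matches the adverse event definitions in section 3.5. The cost is one sentence, with no change to sample size, data collection, trial conduct or the primary analysis.

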### Missing data handling

7.1.

The principle of intention-to-treat analysis will be used herein. Participant data may be missing due to study withdrawal, loss to follow-up, excessive side effects, or other reasons. Missing data will be processed by multiple imputations, with the imputation times set to 5 and 50 maximum iterations. A predictive mean matching model will be used for imputing continuous variables, and a logistic regression model for imputing categorical variables. After imputation, the final data will be analyzed.

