### Sample size calculation

2.6.

The sample size was calculated based on the primary outcome. According to previous studies, the incidence of severe postoperative pain in patients undergoing TKA with multimodal analgesia is 25–40% (16, 17). Considering variance in multimodal analgesia and follow-up times, we reviewed the records of 20 patients who had undergone unilateral TKA in the past month. With multimodal analgesia, 48% of patients reported severe pain (NRS ≥ 7 points) within 12 postoperative hours. Therefore, we assumed that the incidence of rebound pain in patients undergoing TKA in the context of multimodal analgesia is 45%. We expect that the incidence of rebound pain in the esketamine group will be at least 35% lower than in the placebo group during the first 12 post-surgical hours. Using Power Analysis and Sample Size version 15.0 (Stata Corp. LP, College Station, TX, United States) and assuming a significance (*α*) level = 0.05 and power (1 − *β*) = 80% determined sample sizes for the esketamine group (*N*_1_) = 160 and placebo group (*N*_2_) = 160. Considering potential withdrawal (10%), a final 356 patients (178 in each group) will be included to achieve the appropriate power to test our hypothesis.

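### Fixing the number of imputations at 5 adds avoidable Monte Carlo error to the primary risk ratio, interval and p-value

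*Protocol article*

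**What the plan says.** Section 7.1 (Missing data handling) of the protocol article sets multiple imputation "with the imputation times set to 5 and 50 maximum iterations". Continuous variables are imputed by predictive mean matching, and for the rest there is "a logistic regression model for imputing categorical variables", which covers the binary primary outcome. The section ends: "After imputation, the final data will be analyzed".

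Section 7 (Statistical methods) puts all randomized participants in the primary analysis by intention to treat: "the relative risk (RR) and 95% confidence interval (CI) will be calculated using the modified Poisson regression model". It also fixes the decision rule: "All statistical tests will be two-sided and *p* < 0.05 will be considered statistically significant". No complete-case analysis is named as primary.

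Section 2.6 (Sample size calculation) raises 160 per group to 178 per group in the sentence that opens "Considering potential withdrawal (10" (per cent). That is an allowance for withdrawals. Nowhere does the article give an expected share of missing 12-hour outcomes.

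**The concern.** Pooled results from multiple imputation are themselves random. The same locked data imputed with another seed give another risk ratio, interval and p-value. The size of that scatter is governed by the fraction of missing information and the number of imputations. With 5 imputations the between-imputation variance is estimated on 4 degrees of freedom, and the average over imputations is taken over only 5 draws.

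The usual defence of 5 is that the estimate loses little efficiency. That concerns the variance of the estimator over repeated trials. It does not say how closely two analysts with the same data would agree on one p-value that is set against a fixed threshold. If the observed result falls near 0.05, they could report opposite primary conclusions for no reason other than the seed.

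**Working it through.** **Inputs from the article.** 5 imputations (section 7.1); 178 randomized per group, placebo incidence 45%, incidence 35% lower with esketamine, 10% withdrawal, two-sided alpha 0.05, 80% power (section 2.6); risk ratio by modified Poisson regression (section 7).

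**Inputs assumed.** Primary outcomes missing at random in 2%, 5% or 10% of each group. The 10% borrows the withdrawal allowance as an upper value.

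**Step 1: the plan's own figure.** Reading 35% as relative, the esketamine incidence is 0.45 × 0.65 = 0.2925. The two-proportion formula gives 147 per group without and 159 with continuity correction, against the stated 160. Then 160 / 0.90 = 177.8, rounded up to 178. The plan's figures reproduce.

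**Step 2: simulation error by formula.** Monte Carlo error of the pooled estimate, as a share of its standard error, is √(FMI / m), where FMI is the fraction of missing information and m the number of imputations. With FMI taken as 0.10:

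- m = 5: √(0.10 / 5) = 0.141
- m = 50: √(0.10 / 50) = 0.045

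**Step 3: simulation on fixed data.** One dataset is held fixed and imputed 20,000 times, changing only the random draws. Each imputation draws the event rate within each group and fills in the missing binary outcomes. The log risk ratio with its robust variance is then pooled by Rubin's rules with a t reference.

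| Missing per group | Observed events, esketamine vs placebo | Complete-case p | m | Central 95% range of p | Seeds with p < 0.05 |
|---|---|---|---|---|---|
| 10% | 55/160 vs 72/160 | 0.054 | 5 | 0.027–0.112 | 36% |
| | | | 50 | 0.044–0.068 | 22% |
| | | | 100 | 0.047–0.063 | 14% |
| 10% | 54/160 vs 72/160 | 0.041 | 5 | 0.020–0.091 | 63% |
| | | | 50 | 0.033–0.052 | 94% |
| | | | 100 | 0.035–0.049 | 99% |
| 5% | 58/169 vs 76/169 | 0.047 | 5 | 0.029–0.079 | 55% |
| | | | 50 | 0.041–0.055 | 75% |
| 2% | 60/174 vs 78/174 | 0.050 | 5 | 0.037–0.069 | 45% |
| | | | 50 | 0.046–0.056 | 42% |

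In the first dataset the simulated ratio of Monte Carlo error to standard error is 0.140 at m = 5 and 0.044 at m = 50, which agrees with step 2. The risk ratio ranges over 0.735–0.794 at m = 5 and 0.755–0.773 at m = 50.

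**Step 4: away from the threshold.** With 47/160 vs 72/160 (29.4% vs 45%, close to the planned effect) and 10% missing, p ranges over 0.002–0.017 at m = 5. Every run is below 0.05.

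**The case against.** The strongest objection is that little will be missing. The primary outcome is recorded within 12 hours of surgery in inpatients who were trained on the pain diary the day before, and ward nurses act on their scores. A withdrawal after 12 hours costs no primary data. This stands, and it limits the size. A reader might infer from section 2.6 that the plan expects 10% of primary outcomes to be missing. It does not say so, which is why 10% serves here only as an upper assumption with lower values beside it.

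Second, the examples were placed near 0.05. Averaged over trials simulated at 45% vs 29.25%, two seeds disagree on significance in about 5% of trials with 5 imputations and under 2% with 50 when 10% are missing. The figures are about 3% and 1% at 5% missing, and under 2% and under 1% at 2% missing. The expected gain is therefore small. It is not nil at the planned effect, because sampling variation alone can bring a trial close to 0.05. It would be wrong to say that the issue arises only if the true effect is smaller than assumed.

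Third, more imputations do not abolish the problem. At m = 50 the first example still straddles 0.05, and for a result almost exactly at 0.05 with 2% missing the share of significant seeds hardly changes (45% vs 42%). This also stands: the gain is a narrower range, not immunity.

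Fourth, the article states neither a seed nor a pooling rule. A reader might count these as faults. They are details that an article may leave to the full protocol or analysis plan, and their absence is no finding. The number 5 is different, because the article states it.

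**Conclusion.** The point holds as a minor one. The stated 5 imputations leave simulation error of about 14% of the standard error if 10% of primary outcomes are missing, against about 4.5% with 50. Near 0.05 this is enough for the seed to decide the verdict; away from 0.05 it is not. The size falls with the share missing, and that share is not given.

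Two stronger readings are not supported. Five imputations do not bias the risk ratio, and nothing here shows an inflated type I error: the fault is reproducibility and a little precision. Nor does the plan contradict itself on this point, since multiple imputation with 5 datasets is a valid procedure.

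The figures rest on outcomes missing at random, imputation on treatment group alone and the unadjusted risk ratio. Predictive covariates in the imputation model would narrow the ranges somewhat.

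**What to change.** In section 7.1, raise the number of imputations from 5 to between 50 and 100 and leave the iteration limit as it is. On the first example this cuts the width of the p-value range from 0.085 (0.112 − 0.027) to 0.024 (0.068 − 0.044) at 50. A seed set before database lock can be stated alongside. The change is one number and seconds of computing, affects no participant, and can be made at any time before the database is locked.

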### Secondary outcomes

3.2.

Incidence of rebound pain within the first 24 postoperative hours.Time to entering the first pain cycle during the first 24 postoperative hours (i.e., time from PACU transfer to initial analgesic intervention).Time to first rebound pain during the first 24 postoperative hours (i.e., time from PACU transfer to first NRS ≥ 7).The modified rebound pain score (MRPS). MRPS = HNRS−LoNRS (PACU) (2), where HNRS (24) is the highest NRS pain score within 24 h after regional nerve block, and LoNRS (PACU) is the lowest NRS pain score while in the PACU.NRS scores at rest (i.e., laying quietly) and exercise (i.e., raising the affected limb ≥5 times to ≥30 cm) at: 1 day before their operation, PACU transfer, the morning of the first postoperative day; during physical therapy on the first postoperative day; the evening of the first postoperative day; the morning of the second postoperative day; and the evening of the second postoperative day. Morning is defined as 8–10 a.m. and evening as 8–10 p.m.The cumulative opioids upon transfer to the PACU and at 12, 24, and 48 postoperative hours. Cumulative opioids includes administration of basic and remedial analgesics, which will be converted to ‘morphine-equivalent dose’ for analyzes.One day before their operation and first postoperative Timed Up and Go test (i.e., time required to stand up from a standard-height armchair, walk forward three meters, walk back to the chair, and sit down).Range of motion [i.e., degree of the affected knee joint from neutral (0°) to maximum flexion] of the active and passive knee joints at 1 day before their operation and on the first postoperative day.Time to discharge (i.e., when the participant can walk from bed to bathroom independently and along the corridor without the help of a walker).Length of stay (i.e., number of days from admission to discharge).Quality of Recover (QOR)-15 scores at 1 day before their operation and the first postoperative day.Blood glucose and cortisol concentration at admission and the first postoperative day.Patient satisfaction at discharge, where 1 point is ‘unsatisfactory’, 2 points is ‘relatively satisfactory’, and 3 points is ‘satisfactory’.

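### The day-1 Timed Up and Go has no result for a patient who cannot walk; if inability is recorded as missing and reflects poor recovery, the imputation rule dilutes a real benefit on this secondary outcome

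*Protocol article*

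**What the plan says.** Section 3.2 (Secondary outcomes) lists the "One day before their operation and first postoperative Timed Up and Go test" and defines it as the "time required to stand up from a standard-height armchair, walk forward three meters, walk back to the chair, and sit down". Table 1 places the postoperative test on POD 1. Neither place gives a result for a patient who cannot perform it.

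Section 7 (Statistical methods) sets an intention-to-treat analysis: "We plan to include data from all the participants assigned to randomized grouping, regardless of intervention, in a intention-to-treat analysis". Single-time continuous outcomes are compared by t-test or Mann-Whitney test, and secondary outcomes are declared exploratory.

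Section 7.1 (Missing data handling) puts all causes of missingness together: "Participant data may be missing due to study withdrawal, loss to follow-up, excessive side effects, or other reasons". It then fixes one treatment for them: "Missing data will be processed by multiple imputations, with the imputation times set to 5 and 50 maximum iterations", and "A predictive mean matching model will be used for imputing continuous variables", with logistic regression for categorical ones. The sensitivity analyses in section 7 concern the primary outcome only.

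**The concern.** A walking time exists only for patients who walk. On the first day after knee replacement, being unable to stand and walk is the worst possible result of the test, not an absence of information. The article makes some inability foreseeable. Its introduction cites severe knee pain in 60% of patients after this operation. Section 3.2 also treats independent walking without a walker as a milestone for discharge, which Table 1 assesses at the discharge visit, after POD 1.

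If such patients count as missing, section 7.1 replaces the worst results with ordinary ones. A treatment that lowers pain should also lower the number of unable patients, so more poor results would be replaced on placebo than on esketamine. Part of any real benefit would then disappear from the comparison, and no planned sensitivity analysis would show it.

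**Working it through.** **The plan's own figure.** The article gives no figure for the Timed Up and Go or for inability. Its sample size reproduces: 45% on placebo and a relative reduction of 35% give 0.45 × 0.65 = 29.25% on esketamine. With two-sided α = 0.05, power 80% and continuity correction, this needs 159 per group (stated: 160), and 160 / 0.90 = 178. The point does not affect these numbers. The simulation uses 178 per arm.

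**Assumptions (none from the documents).** The day-1 score is standardised, with higher meaning slower. Its correlation is 0.4 with baseline and 0.5 with a pain score. The true benefit is 0.30 SD. A patient is unable when the score exceeds a cut-off z, set so that 5%, 10%, 20% or 30% of placebo patients are unable. The esketamine rate is then 1 − Φ(z + 0.30); for 5%, 1 − Φ(1.645 + 0.30) = 2.6%. No other missingness is simulated.

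**Method.** Predictive mean matching on arm, baseline and pain, with 5 donors and the planned 5 imputations. Pooling is by Rubin's rules: Q is the mean of the five differences, T = W + (1 + 1/5)B, and the test rejects when |Q/√T| > 1.96. The comparator is a Mann-Whitney test with unable patients ranked worst. There are 400 runs per setting, so a power near 80% has a simulation error of about √(0.8 × 0.2 / 400) = 2 points. Dilution = 1 − imputed / complete.

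| Unable, placebo / esketamine | Complete-data difference (SD) | Imputed difference (SD) | Dilution | Power, complete data | Power, imputed | Power, worst rank |
|---|---|---|---|---|---|---|
| 5% / 2.6% | 0.306 | 0.271 | 11% | 82% | 78% | 79% |
| 10% / 5.8% | 0.300 | 0.244 | 19% | 82% | 75% | 82% |
| 20% / 12.6% | 0.301 | 0.205 | 32% | 82% | 65% | 77% |
| 30% / 20.7% | 0.298 | 0.177 | 41% | 80% | 57% | 80% |

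**Mechanism.** In a second set of 600 runs, the unable patients' true mean was 2.052 SD at 5% unable, and the imputed mean was 0.535 SD. At 20% unable these were 1.373 and 0.024 SD. Baseline and pain move the imputed values part of the way, but no imputed value can exceed the worst observed one.

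**Rank scale.** If the Mann-Whitney test is used after imputation, the loss is smaller. The probability that a placebo patient is slower than an esketamine patient is 0.583, 0.578, 0.573 and 0.570 after imputation, against 0.586, 0.583, 0.583 and 0.582 with worst ranks. As a loss of the excess over 0.5, for example 1 − 0.070/0.082, that is about 3%, 6%, 12% and 15%.

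**Limiting cases.**
- No treatment effect: imputed differences are 0.001 to 0.006 SD, and rejection rates are 5.2%, 6.2%, 4.5% and 6.2%, with a simulation error of about 1.1 points. There is no sign of bias or inflation.
- Inability unrelated to the score: 0.304, 0.296, 0.301 and 0.304 become 0.304, 0.297, 0.299 and 0.299. There is no dilution.

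**Another parameterisation.** With 160 per arm, a log-time difference of −0.15, SD 0.5 and inability only partly determined by the score, the imputed difference is −0.123, −0.107 and −0.096 at 10%, 20% and 30% unable on placebo. Dividing by −0.15 gives dilution of 18%, 29% and 36%.

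**The case against.** The strongest reply is that the article never says an unable patient is recorded as missing. Section 7.1 does not name inability, and its coding may sit in the case report form, the assessors' procedures or the analysis plan, none of which is shown. This stands as a condition on the finding. It does not remove it, because the article does state a rule for missing continuous values regardless of cause and defines the outcome so that an unable patient has no value.

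Second, the bias is conservative, needs both a true benefit and outcome-related inability, and touches an exploratory outcome. All of that stands. The simulation also makes inability depend on the score by construction, so it shows what follows from that assumption and not how often it occurs. At 5% unable, the power loss of about 4 points is small.

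Third, time to independent walking and the day-1 QoR-15 partly capture failure to mobilise. They do, but they do not repair the Timed Up and Go comparison.

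A reader might extend the point in three ways that the documents do not support.
- *Exercise NRS is affected in the same way.* It requires "raising the affected limb ≥5 times to ≥30 cm" and has no entry for inability. But NRS is bounded, and patients who complete the raises can give the top score, so matching can return the worst value. Nothing was simulated for this outcome.
- *The exercise score at PACU transfer should be dropped.* Residual block may prevent leg raising in a patient with little pain, so the direction of any bias is unclear.
- *Imputation hides sedation-related inability on esketamine.* Section 2.12 ends the infusion at knee suture, the introduction gives ketamine a half-life of 2 to 4 hours, and the test is on POD 1. Nervous-system complications are separate safety outcomes in section 3.3.

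**Conclusion.** The point holds for the POD 1 Timed Up and Go, conditionally. If inability is recorded as missing and is related to poor recovery, predictive mean matching assigns completers' times to patients who could not walk and shrinks a true benefit. For an assumed benefit of 0.30 SD and 5% to 30% unable on placebo, the mean difference loses roughly 10% to 40%, and power falls from about 80–82% to between 78% and 57%. On the Mann-Whitney scale the loss is about 3% to 15%. The documents give no inability rate, so these are ranges and not estimates for this trial.

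A reader might infer that the rule could produce a false positive or weaken the main result. It does neither: with no treatment effect no bias appears, and the primary outcome comes from the pain diary and needs no walking test. This is a cheap improvement to one exploratory secondary outcome.

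**What to change.** In section 3.2, make *unable, with reason* a recorded result of the Timed Up and Go, judged without knowledge of the arm. In the analysis, give all unable patients the same worst rank in the Mann-Whitney test already planned, and report the proportion able in each arm beside it. In section 7.1, limit multiple imputation of this outcome to values missing for reasons unrelated to ability.

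For exercise NRS, only record *unable, with reason*. Do not treat inability caused by residual block as a worst pain score, and leave the PACU time point in place.

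The cost is one case report form field and a sentence in each of the two sections. The reason has to be captured at the visit, since it may not be recoverable later. The small downside is that the effect becomes rank-based, combining ability and speed, and is no longer a mean difference in seconds; the write-up should say so.
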